### Data monitoring plan

Because this is a behavioral study that does not involve any testing of medications, or any type of procedure that is outside the usual care provided to HIV-positive individuals, the study team’s role in monitoring patient safety will be limited to mandated adverse event (AE)/serious adverse event (SAE)/unanticipated problems reporting, alerting the site to unexpected test findings or conditions identified during participant participation, and reporting to the appropriate authorities any suspected abuse or maltreatment of adolescent participants. AEs will include clinical reactions to treatment and blood draws related to the study, as well as any reported stigma or physical and/or mental harm as a result of participation in the study, including disclosure of HIV status. All AEs will be recorded on designated forms by the on-site study coordinator and rated for both severity and seriousness. Any SAE or unanticipated event that occurs during the course of the study will be reported immediately to the PI and reported to the IRBs within one week of their occurrence. When necessary, the local study team can arrange for hospitalization and treatment at the nearest district hospital, in addition to referral to mental health services if required. Any events deemed by the study team to be possibly related to the study will be carefully reviewed and, if necessary, modifications to the protocol or informed consent will be made in order to protect the safety of study participants.

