### Pre-intervention period and randomization (Month 1)

Once enrolled, each participant will be provided with a WPC (AdhereTech Gen2 device, AdhereTech, Inc., New York, NY, USA) and instruction on correct use. Each participant will select one tablet, either a single antiretroviral drug or in some cases, a combination tablet, to be stored in the WPC. While participants continue to receive care as usual, we will collect their adherence data using their WPCs. After one month, the study statistician will assess adherence over the month and randomize participants within adherence strata (optimal ≥ 95% vs sub-optimal < 95% on-time doses, defined by a ± 2-h window) to intervention or comparison group using a block randomization approach and one set of sequentially numbered opaque sealed envelopes containing computer-generated random assignments for each stratum. The statistician will provide the study coordinator with the participants’ assignments electronically via an encrypted data transfer system.

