### Intervention period (Months 2–7)

The real-time feedback intervention will be implemented as described above. While comparison participants will not receive the reminders or adherence-informed counseling, they will continue to provide adherence data via their WPCs.

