### RCT data collection procedures

Once enrolled, RCT participants will provide study data as follows:*Sociodemographic data and SDT constructs*: upon enrollment, all participants will complete a baseline survey with the site coordinator which will cover: age; gender; ethnicity; education; school-going behaviors; family routines; scales for each of the SDT constructs; self-efficacy; stigma; a child depression index; and a strengths and difficulties index.*Continuous adherence data in Months 1–7*: data on WPC openings will be transmitted continuously via 3G cellular network to a central server, which will automatically download data to a password-protected web-based database that investigators can access as needed for analysis. This system will provide adherence data for each participant. We will also collect data on the frequency of reminder messages sent to each participant by type of reminder, for intervention participants only.*Continuous data on signal lapses*: during Month 1, we will investigate all WPC signal lapses lasting ≥ 48 h by phone call to the participant and determine whether a lapse was due to technical failure (battery failure, forwarder malfunction) or behavioral cause (missed dose, intentional non-use).*Device utilization questionnaire*: we will administer a survey on adolescents’ experience using the WPC at the Month 1 visit for all participants.*Monthly check-in questionnaire*: a brief questionnaire will be administered to all participants to collect data on: whether adherence counseling occurred (yes/no); who was responsible for WPC management; and the occurrence of any major life events (including status disclosure).*Month 7 follow-up questionnaire*: a final survey will be administered to all participants at the end of the intervention period, similar to that completed at baseline, with the addition of a brief quantitative and open-ended questionnaire asking about experience with the WPC, including convenience of use, storage, and potential stigma/loss of confidentiality.*Biological samples*: all participants will provide blood samples for CD4 count and VL tests at Month 1 (pre-randomization) and Month 7 (post-intervention period). Standard of care in Vietnam is CD4 count testing every three months and VL testing every six months free of charge to patients, but VL tests are rarely done due to cost. We will try to time enrollment to align with patients’ blood draw schedule such that, in general, no additional blood draws will be necessary for VL or CD4 tests, but some patients may be enrolled at a time when they are not due for a regular CD4 test; these patients will require an extra blood draw for the study at enrollment. All samples will be identified only by the patient’s study ID to ensure confidentiality. Data will be provided to the clinic for addition to participants’ charts in order to inform treatment. All extra testing costs will be paid for by the research project budget.

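### The adverse event definition requires attribution to the study, so non-serious harms can be screened out before logging in an unmasked setting (minor, safety ascertainment only)

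*Protocol article*

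**What the plan says.** All references are to the Protocol article, Methods.

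- **Data monitoring plan, definition.** Besides study-related clinical reactions, adverse events are to include "any reported stigma or physical and/or mental harm as a result of participation in the study, including disclosure of HIV status".
- **Data monitoring plan, recording.** "All AEs will be recorded on designated forms by the on-site study coordinator and rated for both severity and seriousness". No relatedness rating is stated.
- **Data monitoring plan, serious events.** The reporting rule covers "Any SAE or unanticipated event that occurs during the course of the study", with no relatedness condition. The section also provides, again without such a condition, for alerting the site to unexpected test results or conditions and for reporting suspected mistreatment of participants.
- **Data monitoring plan, review.** "Any events deemed by the study team to be possibly related to the study will be carefully reviewed", with changes to protocol or consent where needed.
- **Pre-intervention period and randomization (Month 1).** "The statistician will provide the study coordinator with the participants’ assignments electronically via an encrypted data transfer system".
- **Intervention period (Months 2–7).** "comparison participants will not receive the reminders or adherence-informed counseling", although they keep using the pill container.
- **RCT data collection procedures.** All participants are asked monthly about "the occurrence of any major life events (including status disclosure"). The baseline survey of all participants covers "stigma; a child depression index; and a strengths and difficulties index", and a similar survey follows at Month 7 with added questions on experience of the container.
- **Dissemination.** Adverse event information, if applicable, goes into the registry results. A larger effectiveness study may be planned if the findings support it.

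**The concern.** The usual order is to record an event when it is reported and judge its relation to the study afterwards. Here the causal judgement is part of the test for being an adverse event at all, so for non-serious harm it comes first. The person keeping the log can know the participant's arm, and neither participants nor care providers are blinded. The section on protection against bias argues that detection bias is not a major concern from electronic adherence measurement and masked laboratory staff. It does not address adverse events.

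The later study-team review can act only on events that have come to its notice. A non-serious harm that nobody traced to the study at the time leaves no entry in the log, and so cannot be reviewed or rated for relatedness.

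What is at stake is how completely harms are seen in adolescents with HIV, for whom stigma and unwanted disclosure are the foreseeable risks of this kind of intervention. The count would also inform any larger study.

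**Working it through.** **Step 1: which events depend on attribution.** Setting the provisions side by side:

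| Event or source | Attribution needed before recording? |
|---|---|
| Serious or unanticipated events | No |
| Suspected abuse; unexpected test results or conditions | No |
| Major life events, including status disclosure (monthly, all participants) | No |
| Stigma, depression, difficulties (baseline and similar Month 7 survey, all participants) | No, but two time points and not an event log |
| Other non-serious physical or mental harm | Yes |
| Other non-serious stigma and disclosure | Yes on the natural reading; the qualifier could instead attach only to harm |

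The gap is the last two rows. The stigma and confidentiality questions added at Month 7 concern the pill container, so they do not close it.

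**Step 2: inputs for size.** The plan gives no adverse event rate, so there is no figure of its own to reproduce. The only documented input is 40 per arm (Sample size and power considerations). Each event left off one arm's log changes that arm's proportion by 1/40 = 2.5 percentage points. The following are assumptions: *b*, the true share of participants with a non-serious harm event (5%, 10%, 20%), and *s*, the share of those attributed to participation (100% to 25%).

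**Step 3: chance that an arm logs no event.** P = (1 − b·s)^40. For example, with b = 0.05 and s = 0.5, (1 − 0.025)^40 = 0.363.

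| b | s = 100% | 75% | 50% | 25% |
|---|---|---|---|---|
| 5% | 13% | 22% | 36% | 60% |
| 10% | 1.5% | 4.4% | 13% | 36% |
| 20% | 0.01% | 0.15% | 1.5% | 13% |

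Events missed per arm at s = 50% are 40·b·0.5 = 1, 2 and 4 at b = 5%, 10% and 20%.

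**Step 4: possible distortion of a by-arm count.** If true harm is equal in the two arms but *s* differs by a gap *g*, the expected false difference is 40·b·g events.

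- g = 0: none.
- g = 10 points: 0.2, 0.4, 0.8 events (0.5, 1, 2 percentage points).
- g = 25 points: 0.5, 1, 2 events (1.3, 2.5, 5 percentage points).

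For comparison, the 95% half-width of a difference in proportions is 1.96·√(2b(1 − b)/40) = 9.6, 13.1 and 17.5 points at the same rates. The false differences are smaller than this in every case.

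**The case against.** The strongest reply is that this is a condensed article. The designated forms are not shown, the abbreviation list mentions a data safety monitoring plan, and logging rules and relatedness ratings usually sit in such documents. The definition says what adverse events will include, which need not be exhaustive. The sentence on reviewing events judged possibly related makes most sense if some logged events are not so judged, and it gives that judgement to the study team. The coordinator is nowhere named as the person who decides attribution. The qualifier may govern only physical and mental harm, leaving stigma unconditional. Several attribution-free routes already exist.

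Most of this stands and limits the point. It does not remove it. The article does not merely omit detail: it states a definition with causation in it, and on either reading of the qualifier physical and mental harm remain conditional. A relatedness field on an unseen form would not recover events that the definition kept off the form.

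A reader might go further and infer that adverse event counts by arm will be biased, because only one arm receives reminders and adherence-informed counseling. The documents do not support that. Control participants also use the pill container, so attributable stigma or disclosure can arise in both arms. Nothing shows that attribution would differ, and no comparison of adverse events between arms is planned.

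**Conclusion.** The point holds as a minor, inexpensive improvement to safety ascertainment. As worded, the definition can keep non-serious physical or mental harm, and probably stigma and disclosure, off the log before anyone rates relatedness, in a setting where the arm can be known. The documents show this risk, not that it occurs.

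The main loss is harm events not seen: about 1 to 4 per arm at assumed rates of 5% to 20% with half attributed. A misleading between-arm conclusion is not the expected result. Even an assumed 25-point gap in attribution gives a false difference of 1.3 to 5 points, well inside sampling error. Apart from the 40 per arm, every rate here is an assumption. Adherence, CD4 count, viral load and sample size are unaffected. Confidence is medium, because the forms and the full safety plan are not shown.

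**What to change.** In the Data monitoring plan, record any reported stigma, physical or mental harm, or unwanted disclosure during the study, in both arms, whether or not it is thought related. Rate relatedness as a separate field beside severity and seriousness. Keep the study-team review of possibly related events as it is.

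I would not build a between-arm disclosure contrast from the monthly check-in item. Status disclosure is undefined there. Because participants were perinatally infected and some may not fully understand their diagnosis, it could include an adolescent learning their own status. Such a contrast would also be unplanned and imprecise.

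The cost is one change to the definition and one added rating, unless the forms already carry it. No new visits are needed. Logging rises slightly, by about 1, 2 or 4 events per arm at assumed rates of 5%, 10% and 20% with half now attributed. The Trial status section reports enrollment as active, so harms before the change may stay unlogged, and the date of the change should be noted when adverse events are reported.

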### Provisions to protect privacy and maintain confidentiality of data

We will ensure the confidentiality of adolescent patients to the greatest degree possible throughout the study. All interactions with participants will occur in closed rooms at the NHP clinic to ensure privacy. Data files, audio files, transcripts, questionnaires, and forms will be kept locked at all times when they are not in use by study personnel. Participants will each be assigned and identified only by a unique ID number, as will their caregivers, whose ID number will be associated with the adolescent for whom they provide care. All paper questionnaires, WPCs, other computer-based data files, and audio recordings will be accessible to named study personnel only, and only in forms without identifying personal identification of any kind other than the unique study ID number. Recordings will be destroyed after the patient completes the study or a final disposition is known. In addition, we will advise intervention participants to select a personal reminder that does not refer to HIV, to help prevent disclosure of HIV status if someone else reads the message. Because some adolescents may not have full understanding of their HIV diagnosis, interview guides and survey instruments will not refer to HIV explicitly but instead will use an appropriate Vietnamese translation of “your disease” when referring to HIV. Electronic data will all be maintained in password-protected files in encrypted folders and the file that links names and study numbers will be stored on computers in a locked office, with access limited to key study personnel. Study results and analyses presented in technical reports, manuscripts, and articles, including qualitative data, will either be presented in aggregate form, or with details removed to prevent identification of individuals.

### Data management and analysis

For all qualitative data, audio recordings will be transcribed, supplemented by written notes, translated into English by a bilingual translator. The English-language transcripts will then be checked by a second bilingual translator and coded and analyzed the transcripts using NVivo™ software. All survey data collected by research assistants for the RCT will be directly entered via tablet into Open Data Kit [59]. The study coordinator will coordinate data retrieval from the web-based server and will back up files weekly on a secure local server at the study office. The data manager will use standard procedures to conduct initial data cleaning, conversion into proper format for data analysis, and recoding. SAS version 9.4 will be used for all data cleaning, management, and quantitative analyses (The SAS Institute, Cary, NC, USA).

### Analytic approach, qualitative analyses (Specific Aims 1 and 3)

The analysis of the formative data collected in Phase 1 and the IDIs at the end of the Phase 2 intervention is by definition descriptive and will not be used to test study hypotheses formally. In Phase 1, our qualitative data will allow us to examine facilitators of and challenges to adherence as perceived by adolescent ART patients and their caregivers and clinicians. In Phase 2, IDIs will help to identify specific barriers to and facilitators of intervention effectiveness by tapping into the “grounded” experiences of adolescent patients who experienced the personalized intervention. For activities in each phase, we will use an iterative approach to: (1) identify themes; (2) build and apply a codebook; and (3) describe thematic characteristics, patterns, and relationships [60–62]. To promote validity and reliability, disconfirming evidence (e.g. negative cases) will be specifically identified. In Phase 1, we will compare adolescents’ responses to caregivers’ responses.

### Analytic approach (Specific Aim 3)

We will calculate the proportion-based key measures described above (enrollment, WPC use, technical failures), analyze reasons for refusal and drop-out, and supplement these findings with qualitative data from the Month 1 questionnaire, IDIs, and field notes. Feasibility and acceptability of *real-time feedback* will be indicated by proportions of: approached eligible patients who enroll; enrolled participants who complete the study; participants who report WPC use is convenient/easy; participants who report serious concerns with WPC or any intervention aspect; and intentional non-use of WPC as % of expected openings. If % technical failure as % of expected openings > 20%, this finding will suggest that the intervention may not be technically feasible.

### Analytic approach (Specific Aim 4)

In accordance with this study aim (to generate preliminary data regarding the efficacy of the real-time feedback package on adherence, CD4 count, and VL), this analysis will be non-confirmatory. We will assess differences between intervention and control in post-intervention proportions achieving optimal adherence, mean adherence, mean CD4, and proportions achieving UDVL, also stratified by optimal or sub-optimal adherence in the pre-randomization period. We will report the following comprehensive set of outcomes, including measures of effect, test statistics, and significance:

#### Adherence

Mean adherence, comparing Month 7 to Month 0, and intervention versus control, and in each month of the intervention;% ≥ 95% adherence comparing Month 7 to Month 0, and intervention versus control, and in each month of the intervention.

#### Clinical markers

CD4 count: comparison of mean CD4 count (SD) and change in CD4 between baseline and endline, and intervention versus control;viral load (VL): % UDVL after the intervention (Month 7), comparison between baseline and endline, and intervention versus control

### General approach

We will calculate descriptive statistics for all study variables (means, ranges, standard deviations, percent data missing, and frequencies, percentages for categorical variables). For adherence, a non-opening for a scheduled dose will be considered a non-adherent dose. Repeated openings within the same scheduled dose time will be excluded. Outcomes will not be imputed for patients who drop out. Patients who drop out before randomization will be excluded in experimental analyses. Sociodemographic and clinical characteristics from baseline will be compared between those randomized and those not randomized to assess representativeness of the final analytic sample, using Cochran Mantel–Haenszel χ^2^ tests for categorical variables and Student’s *t* tests for continuous variables. After randomization, we will compare dropout rates and characteristics of patients who drop out between study arms to assess potential for bias using the same statistical tests. All randomized participants will be included in analyses. We will perform both intention-to-treat (ITT) and per-protocol analyses.

For the main dichotomous outcome (% ≥ 95% adherence after the intervention [Month 7]), risk differences and 95% confidence intervals will be calculated. UDVL will be similarly treated as a secondary dichotomous outcome. We will then construct multivariate regression models to adjust for key baseline variables such as gender, using high adherence as the outcome, and intervention group as the primary predictor. Other variables found to be significantly associated with high adherence in bivariate logistic models will be added using forward-stepwise and forced entry techniques. We will also conduct stratified analyses based on gender and other attributes, although we may only have statistical power to detect trends. For continuous outcomes (change in adherence and CD4 count), we will use paired t-tests and General Linear Models to test for differences before and after intervention, then use similar multivariate approaches as described above. To examine interrelationships among adherence and the constructs of our theoretical model, stigma, and other psychosocial measures, we will generate bivariate Pearson correlations and conduct exploratory path analysis.

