### Efforts to protect against standard risks of bias in unmasked trials

Although the nature of our intervention does not allow for blinding of trial participants or care providers, we have put into place the following protections. To protect against *selection bias*, we are using a stratified block randomization technique (as noted above) including allocation concealment via sequentially numbered, sealed, opaque envelopes. Due to the nature of the intervention, which involves clinician counseling, it is not possible to employ blinding, so our findings are at some risk of *performance bias*, although we are providing extensive training to care providers and study personnel to encourage them to standardize their interactions with all participants, with the sole exception of the intervention counseling component.

Our primary adherence outcomes for both intervention and control participants are measured using an electronic adherence monitoring device, an objective measure of adherence that does not involve human knowledge of allocation. Lab personnel who conduct CD4 and viral load processing are also not aware of allocation and have no direct contact with study personnel or participants. We believe that *detection bias* is therefore not of major concern to the study. As for *attrition bias*, we do not expect a great degree of loss to follow-up, withdrawals, or missingness for measures in this short, intensive study, but in addition to comparing background characteristics of those who withdraw or are lost to follow-up, to quantify the impact of missingness that may be non-random and possibly related to (for example) depression (non-ignorable missingness), we will conduct sensitivity analysis using ISNI methods. As noted above, we will conduct ITT and per-protocol analyses for comparison but will prioritize ITT in our reporting of findings.

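### Randomisation is stratified by baseline adherence, but the main risk difference is, on a natural reading, crude; naming the stratum in the pooled estimate would recover precision at no cost if the stratum is prognostic

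*Protocol article*

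**What the plan says.** All references are to the protocol article.

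- **Randomisation.** Under Pre-intervention period and randomization (Month 1), the statistician will "randomize participants within adherence strata (optimal ≥ 95% vs sub-optimal < 95% on-time doses, defined by a ± 2-h window"). The section on protection against bias confirms it: "we are using a stratified block randomization technique (as noted above").
- **Main analysis.** Under General approach, for the proportion with at least 95% adherence at Month 7, "risk differences and 95% confidence intervals will be calculated". Undetectable viral load (UDVL) is handled the same way as a secondary outcome.
- **Adjustment.** The next step reads: "We will then construct multivariate regression models to adjust for key baseline variables such as gender". Further variables enter if they are significantly associated with high adherence in bivariate logistic models, by forward-stepwise and forced entry. The stratum is not named.
- **Use of the strata.** Under Analytic approach (Specific Aim 4), arm comparisons are "also stratified by optimal or sub-optimal adherence in the pre-randomization period". The same section calls the efficacy analysis non-confirmatory, but promises effect measures, test statistics and significance.
- **Sample size.** 40 per arm, two-sided alpha 0.05, and at least 80% power for a 29-point difference. The reference rates are 87.3% versus 51.8%, from an earlier study in adults.

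**The concern.** Balancing a prognostic factor by design removes its between-stratum variation from the arm comparison. A two-sample standard error that ignores the factor still counts that variation, so it is larger than the true sampling variability. Here the factor is the outcome itself, measured some months earlier with the same device and the same 95% cut-off, so it is a natural candidate for a strong predictor.

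The article does not leave covariate choice open. It fixes a rule under which the randomisation factor enters only if it passes a significance screen in at most 80 participants. Because the screening models are logistic, the adjusted result may also be an odds ratio, which would leave the risk difference itself crude.

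At stake is precision in a small trial whose findings, under Dissemination, may lead to a larger effectiveness study.

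**Working it through.** **1. The plan's own figure.** Inputs from Sample size and power considerations: 40 per arm, control rate 0.518, difference 0.29 (so 0.808 in the intervention arm), two-sided alpha 0.05.

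- Unpooled SE = √[(0.518×0.482 + 0.808×0.192)/40] = √(0.4048/40) = 0.1006.
- Pooled SE, with mean rate 0.663 = √(2×0.663×0.337/40) = 0.1057.
- Power (pooled test) = Φ[(0.29 − 1.96×0.1057)/0.1006] = Φ(0.82) = 79.5%. The unpooled version gives 82.2%.
- The detectable difference at 80% power is 29.2 points.

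The stated 29 points therefore reproduces, and it is an unstratified two-proportion calculation.

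**2. Assumptions for the stratified analysis.** The documents give no stratum shares, stratum-specific rates or Month 1 to Month 7 correlation. Assumed: overall rates of 51.8% and 80.8%; 30% or 50% of participants in the optimal stratum; a control-arm gap between strata of 0, 20, 40 or 60 points, with a smaller gap in the intervention arm whenever it is above 0; arms exactly balanced within strata.

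**3. One case by formula.** With w_s the share of stratum s, the stratified variance is Σ w_s[p_Cs(1−p_Cs) + p_Ts(1−p_Ts)]/40. Take a 50:50 split and a 40-point gap: control 0.718 and 0.318, intervention 0.928 and 0.688.

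- Control: 0.5×(0.718×0.282 + 0.318×0.682) = 0.2097.
- Intervention: 0.5×(0.928×0.072 + 0.688×0.312) = 0.1407.
- SE = √[(0.2097 + 0.1407)/40] = 0.0936, against 0.1006 crude: a ratio of 1.075.

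**4. Simulation, 200,000 runs per scenario.** Ranges cover the 30% and 50% splits. Power is at 51.8% versus 80.8%. CMH is the Cochran-Mantel-Haenszel test.

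| Control-arm gap | 95% CI width, crude | 95% CI width, stratified | Crude wider by | Crude coverage | Power, crude | Power, CMH | Type I error, crude |
|---|---|---|---|---|---|---|---|
| 0 | 0.389 | 0.384 | 1% | 94.1% | 79.5–79.7% | 79.6–79.8% | 5.6% |
| 20 | 0.389 | 0.377–0.379 | 3% | 94.4–94.5% | 79.9% | 80.8% | 5.2% |
| 40 | 0.389–0.390 | 0.357–0.363 | 7–9% | 95.5–95.8% | 80.9–81.1% | 84.4–84.9% | 3.8–4.0% |
| 60 | 0.390–0.391 | 0.320–0.340 | 15–22% | 96.8–97.5% | 82.2–83.2% | 87.5–91.8% | 1.7–2.2% |

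The type I error of the CMH test stays at 4.8–5.6%.

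A caution on the widths: the simple stratified Wald interval is itself slightly short at this sample size, with coverage of 93.7–94.0%. That accounts for the 1% difference at a gap of 0, and for part of the difference elsewhere. In the case in step 3 the formula gives 7.5%, where the simulated widths give 0.390/0.357 = 1.09.

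**5. A second model.** Monthly adherence was generated from a latent logit-normal variable (4,000 runs), with an assumed Month 1 to Month 7 phi of 0.51, 0.38 or 0.25. Crude power was 84%, 81% and 81%; stratified power was 89%, 85% and 82%. Crude type I error was 2.3%, 4.2% and 5.0%. The pattern agrees with step 4.

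**The case against.** **The crude estimator is inferred.** The article never says unadjusted, names no weighting, and is a condensed account with no analysis plan shown. This stands in part. The crude reading rests on the order of the text, in which adjustment follows the risk difference. But the article does state a covariate rule, and that rule leaves the randomisation factor to a significance screen. That is a choice made in the article, not a detail left out.

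**The strata are used.** They are, under Aim 4. Those are additional results within strata, though. With an assumed 20 per arm per stratum and rates of 51.8% and 80.8%, each interval is about ±1.96×√(0.4048/20) = ±28 points, so they cannot stand in for a pooled estimate.

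**The screen would usually admit the stratum when it matters.** If baseline adherence is screened, the expected chi-square is about 80×phi²: 20.8, 11.6 and 5.0 at phi 0.51, 0.38 and 0.25. The chance of p<0.05 is then about 99%, 92% and 61%. This weakens the concern for the adjusted model, where gender is only an example ("to adjust for key baseline variables such as gender"). It does not reach the risk difference that comes first.

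**Two stronger readings do not hold.** A reader might infer that the trial is underpowered as analysed. It is not: the 29-point figure was derived without stratification, and crude power stays at 79.5–83.2% in every scenario of the first simulation. A reader might also infer that the crude interval is always conservative. At gaps of 0–20 points its coverage is 94.1–94.5%, slightly below nominal; conservatism appears at 40 points or more, and a conservative interval is still valid.

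**Stakes are limited.** The efficacy analysis is declared non-confirmatory. This stands, and it lowers the importance of the point.

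**Conclusion.** The point holds as a free improvement, not as an error that invalidates the result. The design will "randomize participants within adherence strata", yet no pooled estimate is tied to those strata, and the factor's place in the adjusted models depends on a significance test.

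The cost is forgone precision: negligible if the strata differ little (0–1 point of power at gaps of 0–20 points), about 4 points of power at a 40-point gap, and 5–9 points at 60. In neither simulation did stratifying reduce power.

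These sizes rest on assumed stratum shares and gaps, and on a control rate taken from adults in another study, whereas this trial selects adolescents with adherence challenges. A clear gap is plausible because the stratum is the baseline version of the outcome, but the documents do not quantify it. No calculation was made for UDVL or CD4; for those the recommendation rests on the general principle alone.

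**What to change.** Amend General approach as follows:

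- Make the main Month 7 estimate a risk difference stratified by the randomisation stratum, with Mantel-Haenszel weights and a stratified 95% confidence interval, or a risk difference standardised from a model that includes the stratum. Choose a variance estimator suited to small strata, given the slight under-coverage of the simple stratified Wald interval.
- Treat UDVL in the same way.
- Force the stratum into all adjusted models, whatever the significance screen shows. For CD4, include baseline CD4 as well.
- Keep the crude risk difference as descriptive, and keep the within-stratum results under Aim 4 as additional.

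The cost is about one sentence of analysis wording. No new data or participants are needed, because the stratum is recorded for everyone at randomisation and the trial already collects baseline CD4.
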